### 2.7. Treatment

#### 2.7.1. Basic Drug Treatment

Combined with their past stroke-related risk factors and current medical histories, all patients will receive secondary prophylactic drug treatment for stroke, including antihypertensive, hypoglycemic, antiplatelet, and hypolipidemic drugs.

#### 2.7.2. Conventional Rehabilitative Interventions

Conventional rehabilitation treatment will be administered 5 days per week, 10 sessions (2 consecutive weeks):Physical therapy [5]: PT will include active and passive activity of affected limb joint, neurodevelopmental therapy, balance function training, antispasmodic treatment, muscle strength training, and walking gait training.Occupational therapy [5]: OT will include therapeutic activities for the upper limbs and hands of the affected side, activities of daily living, and training for the use of auxiliary equipment.

PT and OT will be performed by professional physiotherapists with at least 5 years of clinical experience. Each patient's pre- and postrehabilitative intervention will be conducted by the same physiotherapist.

#### 2.7.3. Experimental Group

The experimental group will receive acupuncture at temporal three-needle 5 times per week for 2 weeks following basic drug treatment and conventional rehabilitative treatment. The details of temporal three-needle therapy are presented in Table 2; the therapy will comply with the Standards for Reporting Interventions in Clinical Trials of Acupuncture (STRICTA) checklist [39].

The temporal I needle will be placed on the hairline 2 cun above the apex of the ear; the temporal II needle and temporal III needle will be placed 1 cun from the temporal I needle on either side in the horizontal direction [13] (Figure 2; the use of the picture has been allowed by the author [name] and the patient). After routine disinfection of the scalp, disposable stainless-steel needles (0.30 × 25 mm) (Huanqiu, Suzhou Acupuncture & Moxibustion Appliance Co., Ltd., Jiangsu Province, China) will be manually inserted at each acupoint. After the acupuncturists insert needles into the acupoints at a certain depth and twist them for a while, patients report conscious sensations, such as soreness and numbness, in the acupuncture location, which indicates needle sensation “De Qi.” To treat motor dysfunction, the needles are rotated at 100 revolutions or more per minute for 1 minute at every 5 minutes over 30 minutes.

#### 2.7.4. Control Group

The control group will receive acupuncture at the MS6 from Qianshencong (EX-HN1) to Xuanli (GB6) [20] following basic drug treatments and conventional rehabilitative treatments. The details of acupuncture at MS6 are presented in Table 2; this treatment will comply with the STRICTA checklist [39] as well.

### 2.8. Outcome Assessment

The outcome measurements include functional connectivity (FC), regional homogeneity (ReHo), amplitude of low-frequency fluctuations (ALFF), the Fugl–Meyer assessment of upper limb (FMA-UL), the modified Barthel Index (MBI), and adverse events. FC, ReHo, and ALFF will be measured by rs-fMRI. The FMA-UL, MBI, and adverse events (AEs) will be assessed by three experienced rehabilitative assessors.

Additionally, the study duration will be 2 weeks. Outcomes will be assessed at baseline and after 2 weeks of intervention. Each subject will have the same assessor for their pre- and posttreatment evaluations.

#### 2.8.1. Primary Outcome

The primary outcome is resting-state FC. Functional brain alterations in this study will be more sensitive than structural MRI and behavioral performances in detecting the neuromodulatory effect of temporal three-needle therapy.

Resting-state FC analyses can assess synchronous activity between brain regions and be used to study the brain in healthy and disease groups on the brain-network level, which will help to understand (a) markers for diseases, (b) paths to investigate disease mechanisms, and (c) predictors of clinical course [40]. Resting-state FC could serve as a biomarker of motor function recovery in stroke patients with hemiplegia [41]. Stronger FC after stroke correlates with better behavioral outcome [42]. Resting-state FC analysis may offer an invaluable approach to explore functional network reorganization in the brain after stroke. In this study, brain FC plasticity within and beyond the sensorimotor network will be measured by rs-fMRI.

#### 2.8.2. Secondary Outcomes

The secondary outcomes including ReHo, ALFF, FMA-UL, and MBI will be measured at the same time points of the primary outcome. Brain regional activity (ReHo and ALFF) will be assessed via rs-fMRI. FMA-UL, MBI, and AEs will be assessed by the abovementioned three experience rehabilitative assessors.

ReHo can be used to explore the consistency of neuronal activity in regional brain areas at resting state, which may be a potential biomarker of the neural substrates associated with hand function following stroke [43] and provide an effective tool for evaluating the efficiency of rehabilitative therapies after stroke [44]. An increase in ReHo value indicates that the consistency of neuron activity tends to be increased.

ALFF can reflect the intensity of the nerve activity of a single voxel and hemodynamic BOLD information on neural activity [45]. In addition to FC, regional ALFF may provide complementary information on the neural mechanism [46]. After brain injury, the blood flow of the brain decreases, and the local ALFF value shows a downward trend.

The FMA-UL is used to only assess motor function of the upper limb in stroke patients. Because the motor function of the upper limb is the most difficult to recover after stroke, we focused on upper limb motor dysfunction in this study. The FMA-UL has been shown to be useful for measuring arm and hand motor function, and 30-item assessment shows a longitudinally stable item difficulty order and is valid for measuring volitional arm motor ability over time [47]. The FMA has a total of 100 points for normal motor function. The maximum score for UL is 66. The evaluation includes measuring reflex activity, flexor synergy, extensor synergy, and movement combining synergies, movement out of synergy, elbow, shoulder, wrist, and hand function, and relates coordination and speed. An ordinal scale applied to each item is used: 0 = cannot be performed, 1 = can be partially performed, and 2 = can be completely performed.

The MBI has shown good properties for measuring disability in stroke patients [48] and is the most prevalent functional outcome scale in stroke trials. The MBI covers 10 domains: feeding, grooming, dressing, bathing, toilet transfers, bowel and bladder continence, ambulation, moving between wheel chair bed and back to the wheel chair, and stair climbing. Each item has five levels, with level 5 representing the greatest independence.

### 2.9. Brain MRI Protocol

Healthy controls will undergo a baseline brain MRI scan, and patients in the experimental group and the control group will undergo brain MRI scans at baseline and after treatment. All brain MRI scans will be performed with a 3.0 Tesla scanner (SIEMENS Skyra, Germany) in the Department of Radiology, Shenzhen Nanshan District People's Hospital. The parameters of the sequences were as follows.

Structure MRI: prior to brain functional imaging scan, T1-weighted images of three-dimensional whole-brain structure in sagittal position will be collected using MPRAGE sequence with the following parameters: repetition time (TR)/echo time (TE) = 2530/2.01 ms, flip angle (FA) = 7°, field of view (FOV) = 256 × 256 mm^2^, matrix = 256 × 256, 176 contiguous axial slices, slice spacing = 0.0 mm, and slice thickness = 1.0 mm.

T2 FLAIR (fluid-attenuated inversion recovery):T2 FLAIR will be collected using a turbo spin echo (TSE) sequence with the following parameters: TR = 8500 ms, TE = 102 ms, and flip angle = 160°.

Rs-fMRI: resting-state functional images will be performed using an echo planar imaging (EPI) sequence with the following parameters: TR/TE = 2000/30 ms, FA = 90°, number of slices = 36, matrix = 64 × 64, FOV = 224 × 224 mm^2^, and slice thickness = 3.5 mm.

### 2.10. Data Collection, Management, and Monitoring

The design, modification, and final confirmation of the case report form (CRF) will be jointly conducted by Shenzhen Nanshan District People's Hospital and researchers. The CRF must ultimately be approved by Shenzhen Nanshan District People's Hospital. Electronic CRF will be utilized for data collection. The data entry will be performed separately by two independent staff.

Specialized data manager will be used to maintain the integrity, validity, and correctness of the data and to fully check the primary and secondary outcomes and security indicators specified in the plan to ensure the accuracy and completeness of these data.

Shenzhen Nanshan District People's Hospital is responsible for data collection, data entry, data verification and query, medical coding, blind audit, data export and transmission, archiving of data, and data management.

### 2.11. Statistical Analysis

#### 2.11.1. MRI Data Analysis

The DPABI toolkit [49] will be used to analyze the image data on MATLAB2016 (MathWorks) to detect any functional changes (FC, ReHo, and ALFF) in brain neuroplasticity due to temporal three-needle treatment. After data preprocessing, data-driven approach will be conducted to explore neuroplastic changes in the two patient groups and the healthy control group. Data-driven approaches can automatically obtain the brain functional network from the data [50]. Independent component analysis (ICA) based on data-driven approaches is not required to assume a priori that the MRI signal can be separated directly into a series of maximally independent components and associated time courses [51, 52] and different components corresponding to the corresponding resting-state network. FDR correction will be used for multiple comparisons to control the false positivity rate. Pearson's correlation analysis will be utilized to study the relationship between the rs-fMRI metrics and behavioral data.

#### 2.11.2. Clinical Behavioral Data Analysis

In this study, statistical analyses will be performed by intent-to-treat (ITT) analysis and per-protocol (PP) analysis. The ITT analysis will include not only all patients with valid results but also randomized patients who were discontinued for a period of time for some reason or transferred to another group. For missing values, we will carry over the last observation results to the endpoint so that the number of patients at the endpoint of each group will be the same as that at the beginning of the trial. The PP analysis will be applied to subjects who adhere to the protocol, have good compliance, and complete the process. When differences in the results exist between the two analyses, the final clinical trial results will be discussed and explained. In this study, only those who received more than 70% of the interventions will be considered satisfied compliance. That is to say, in total number of the 10 treatments, subject missing more than 3 treatments will be excluded from the PP analysis due to violation of the protocol.

All differences in the baseline demographic and clinical characteristics between the two patient groups will be analyzed with the chi-squared test or Fisher's exact test for categorical data and with the *t*-test or Wilcoxon rank-sum test for continuous values. Continuous variables will be shown as the means, SDs. Categorical variables will be described as frequencies or percentages. 

All tests will be two-sided, and a *p* value <0.05 will be considered statistically significant. If the difference of the primary endpoint between the experimental group and the control group was statistically significant, the results of the experimental group are superior to that of the control group, and the intervention method could be considered as effective. Therefore, we firstly set the type I error of the primary endpoint at 0.05. If significant, we then go to test the secondary endpoint at 0.05 type I error.

The changes in the FMA and the MBI between pre- and postacupuncture therapy will be analyzed using repeated measures analysis of variance (ANOVA), This analysis will be used to compare differences and to examine the group effect, time effect, and time-group interaction effect.

A post hoc test will be conducted. Within-group differences between pre- and posttreatment will be compared using the paired *t*-test or Wilcoxon signed rank test for continuous data. 

AEs will be tabulated and summarized using descriptive statistics. The AEs incidence of each group will be confirmed as evaluation index, and the computation formula is as follows: AEs incidence% = (number of AEs/total number of cases in this group) × 100%. The current version of STATA 12.0 statistics (StataCorp, Texas, USA) will be used for statistical analyses.

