#### 2.4.3. Dropout Criteria

During the trial period, participants meeting the following criteria will be excluded from the study: (1) occurrence of serious adverse events; (2) missing more than 3 of 10 acupuncture treatment sessions; (3) important violations in the protocol implementation; or (4) withdrawal from the study in light of the participants being unwilling to continue.

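### With one post-treatment assessment, the LOCF rule gives every patient without a final FMA-UL or MBI score a change of exactly zero, and the dropout rule does not say whether excluded patients are still assessed

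*Protocol article*

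**What the plan says.** Four statements in the protocol article bear on this.

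- **Dropout Criteria (2.4.3):** during the trial, "participants meeting the following criteria will be excluded from the study". The first two criteria are "1) occurrence of serious adverse events; (2) missing more than 3 of 10 acupuncture treatment sessions" and the third is "3) important violations in the protocol implementation". The fourth is withdrawal by a participant who does not want to continue.
- **Outcome Assessment (2.8):** "Outcomes will be assessed at baseline and after 2 weeks of intervention". Table 1 agrees, with one pre-treatment and one post-treatment column for FMA and MBI.
- **Clinical Behavioral Data Analysis (2.11.2), population and missing data:** "The ITT analysis will include not only all patients with valid results but also randomized patients who were discontinued". Then "For missing values, we will carry over the last observation results to the endpoint", with the purpose given as "so that the number of patients at the endpoint of each group will be the same as that at the beginning of the trial".
- **Same section, analysis:** "The changes in the FMA and the MBI between pre- and postacupuncture therapy will be analyzed using repeated measures analysis of variance (ANOVA", with group, time and interaction effects. A per-protocol (PP) analysis leaves out patients who missed more than 3 of the 10 treatments, which is also the second dropout criterion.

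**The concern.** Carrying an observation forward assumes that there is a post-baseline observation to carry. Here there is none, so the rule becomes baseline carried forward. A patient without the final score is recorded as having made no progress over two weeks of physical therapy, occupational therapy and needling. Patients enter between 2 weeks and six months after stroke, and both arms get active treatment, so zero is a poor default.

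The dropout criteria decide how many such patients there will be. Three of the four (serious adverse event, many missed sessions, protocol violation) do not in themselves prevent a patient from being scored. If exclusion from the study ends assessment, the protocol produces missing data that it could have avoided. It also weakens the planned ITT-versus-PP comparison: for a patient removed after missing more than 3 sessions, the two analyses would differ only by the imputed zero.

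At stake is the ITT comparison of FMA-UL and MBI. Unequal losses bias it against the arm that loses more patients, and equal losses dilute a true difference.

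**Working it through.** **No plan figure to reproduce.** Section 2.2 takes 20 per arm from published studies. It gives no effect size, SD or dropout rate.

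**Step 1: what LOCF imputes.** The visits are baseline (Y0) and post-treatment (Y1). If Y1 is missing, the last observation is Y0, so the imputed change is Y0 − Y0 = 0. This needs no assumption.

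**Step 2: how the zero enters the test.** With two visits, the time-by-group test in the repeated measures ANOVA is equivalent to a t-test on change. Each imputed zero therefore enters the treatment comparison directly.

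**Step 3: effect on the estimate.** Let pE and pC be the shares lost, and DE and DC the true mean gains. Assume that lost patients would have gained their arm's mean. Then

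LOCF difference = (1 − pE)·DE − (1 − pC)·DC.

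All gains and loss rates below are assumptions; n = 20 per arm is from section 2.2.

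| True gains (E, C) | Lost (E, C) | Calculation | LOCF difference | True difference |
|---|---|---|---|---|
| 8, 8 | 1/20, 2/20 | 0.95·8 − 0.90·8 | 0.4 | 0 |
| 8, 8 | 1/20, 5/20 | 0.95·8 − 0.75·8 | 1.6 | 0 |
| 10, 6 | 2/20, 2/20 | 0.90·10 − 0.90·6 | 3.6 | 4.0 |
| 10, 6 | 4/20, 4/20 | 0.80·10 − 0.80·6 | 3.2 | 4.0 |

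Reversing the loss pattern in the first two rows reverses the sign.

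**Step 4: effect on the test.** This adds an assumed SD of change of 5 points; error rates come from simulation at a nominal two-sided 0.05.

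- Equal gains of 8, losses 1/20 versus 5/20: type I error about 0.12.
- Equal gains of 6, losses 4/20 versus 0/20: about 0.11.
- Equal gains of 6, losses 4/20 versus 1/20: about 0.07.
- Equal gains of 6, losses 2/20 in each arm: about 0.035, so no inflation.
- True gains 10 versus 6, losses 4/20 in each arm: power falls from about 0.69 to about 0.39.

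**Step 5: effect on precision.** With 1/20 and 5/20 lost, 40 − 6 = 34 changes are observed but 40 are analysed. The zeros also add spread. At 20% loss the variance of change is 0.8·25 + 0.8·0.2·D², that is 36.0 for D = 10 and 25.8 for D = 6. The pooled SD is then √30.9 ≈ 5.56 instead of 5. The sample is overstated and the spread altered, so the standard error does not describe the data collected.

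**The case against.** Several points on the other side carry weight.

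- **Scope.** The LOCF rule stands in the section on clinical behavioural data, and FMA-UL and MBI are secondary. Secondary endpoints are tested only if the primary is significant, so the rule cannot create a false primary result. This stands and limits the severity.
- **Primary outcome.** A reader might infer that the primary functional connectivity result is left on selected completers. The article does not support that: section 2.11.1 states no missing-scan rule and no MRI analysis set, and such detail may lie in a fuller document.
- **Meaning of exclusion.** A reader might also take it as settled that excluded patients go unassessed. That is the most natural reading of exclusion from the study under a dropout heading, but the text does not say it. Section 2.11.2 uses the same session trigger only to define the PP set and keeps discontinued patients in ITT. The two sections need reconciling; neither proves that assessment stops.
- **Size.** Treatment lasts two weeks, patients are blinded, and Table 2 gives both arms the same needling details and regimen, so a large imbalance in losses is not the obvious expectation. At 1/20 versus 2/20 the false difference is 0.4 points on a 66-point scale. Patients lost after serious adverse events may also gain less than their arm's mean, which would make the bias smaller than the formula gives. Both points are fair.
- **Existing safeguards.** Keeping all randomised patients is a proper ITT aim, and the plan undertakes to discuss ITT/PP differences. But PP drops the affected patients, so it cannot show what their outcomes were.

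What remains is that the stated imputation rule, with the stated visits, returns zero for every missing endpoint.

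**Conclusion.** The point holds for FMA-UL and MBI and should be fixed; it is not a demonstrated threat to the primary outcome. That LOCF equals baseline carried forward is certain from the visit schedule. Its size depends on how many final scores are missing and how unevenly. Under the stated assumptions, the false difference runs from 0.4 to 1.6 points when true gains are equal, and a true 4.0-point difference falls to 3.2 at 20% loss in each arm. The direction is not fixed in advance. If no final scores are missing there is no effect. With 20 per arm, each patient lost is 5% of an arm.

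The dropout rule and the ITT definition must be reconciled because together they leave open how many endpoints will be imputed. Both rules are written in the article, so this is not detail left to an analysis plan. A later plan could change the imputation method but could not recover assessments that were never made.

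**What to change.** **Section 2.4.3.** State that the listed events end per-protocol status, not outcome assessment. Patients who still consent and can be assessed have the planned post-treatment assessments and stay in the ITT set. Rules on continuing treatment are left as they are. Continued assessment would also preserve the second MRI.

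**Section 2.11.2.** Replace LOCF for FMA-UL and MBI with a likelihood-based longitudinal model of the baseline and post-treatment scores, or with multiple imputation using arm, baseline score and time since stroke. Add a delta-shift sensitivity analysis, in which imputed values are moved by stated amounts, for patients who withdraw or cannot be assessed. Baseline carried forward may remain, at most, as a further sensitivity analysis.

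**Cost.** A wording amendment, already planned assessments kept for a few patients, and slightly more analysis work. The trial is still recruiting, so the change can still prevent avoidable missing scores.

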Because the study design is a superiority trial and stroke patients conventionally receive acupuncture at the scalp acupoint in current clinical practice in China, placebo (sham) stimulation or a blank control may violate the patient willingness. This trial will choose Dingnieqianxiexian (MS6) in the International Standardization Scheme for Scalp Acupuncture Points as the positive comparator in the control group. MS6 is an international standardized scalp acupoint, which refers to a diagonal line from Qianshencong (EX-HN1) to Xuanli (GB6) [20], and is projected to the precentral gyrus [21]; it is responsible for the autonomous movement of the limbs [20]. Studies have indicated that, on the basis of body acupuncture, temporal three-needle therapy is superior to acupuncture at MS6 with respect to daily life activities [22], motor function [22], and motor-related sensory disturbances [19].

However, the central mechanism of temporal three-needle therapy on stroke recovery remains unclear, especially in neuroimaging. From the last several years, with the rapid development of medical imaging technology, magnetic resonance imaging (MRI) has gradually become one of the main methods for studying the mechanism of acupuncture. Resting-state fMRI (rs-fMRI) only requires the subjects to stay still and close their eyes while scanning and keep their body as immobile as possible without thinking about anything. Rs-fMRI reflects intrinsic functional patterns and the spontaneous activity of the brain's cortex [23], which is a useful technique for studying the mechanism of acupuncture [24]. In this trial, we plan to apply rs-fMRI to explore the central mechanism of temporal three-needle treatment.

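### The success rule turns any significant two-sided FC difference into a claim that the experimental arm is superior and the therapy effective, with no required direction and before motor function is tested

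*Protocol article*

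**What the plan says.** The decision rule is in section 2.11.2 of the protocol article. The general condition is "All tests will be two-sided, and a *p* value <0.05 will be considered statistically significant". The rule follows: "If the difference of the primary endpoint between the experimental group and the control group was statistically significant", then "the results of the experimental group are superior to that of the control group, and the intervention method could be considered as effective". The same paragraph goes on to test the secondary endpoint at 0.05 if the primary endpoint is significant.

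Section 2.8.1 names the endpoint: "The primary outcome is resting-state FC". Its scope is wide: "brain FC plasticity within and beyond the sensorimotor network will be measured by rs-fMRI". Section 2.11.1 adds a data-driven analysis (independent component analysis) with FDR correction for multiple comparisons. The closest the article comes to a direction is a background sentence in section 2.8.1: "Stronger FC after stroke correlates with better behavioral outcome". Nothing links that sentence to the success rule.

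FMA-UL and MBI are secondary outcomes (section 2.8.2). MS6 acupuncture serves "as the positive comparator in the control group" (section 1), and both patient groups also receive drug treatment and rehabilitation (section 2.1).

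**The concern.** The rule takes two steps that its condition does not support.

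- **From significant to superior.** A two-sided test rejects in either tail. The condition mentions only significance, so a result favouring MS6 satisfies it too. For a clinical scale the good direction is obvious. For FC it is not: a data-driven search inside and outside the sensorimotor network can find rises in some connections and falls in others.
- **From superior to effective.** The word is reached from FC alone. FMA-UL and MBI, the trial's measures of upper-limb motor function and daily living, are tested afterwards and cannot alter it. Because the comparator is active, a significant result shows an FC change that differs from the one under MS6. It does not by itself show a motor benefit.

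At stake is the headline conclusion. Followed literally, the rule allows a claim of superiority and effectiveness that the data need not support.

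**Working it through.** **Inputs from the protocol article**
- Two-sided alpha 0.05 (section 2.11.2).
- 20 patients per group, 1:1 (sections 2.1 and 2.2).
- No FC effect size, SD or power is given (section 2.2).

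**Assumptions made here**
- One FC summary per patient, compared by a two-sample t-test.
- Standardized differences d of 0.2, 0.5 and 0.8 in favour of MS6, chosen only to show a range.

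**Step 1. Reproduce the stated alpha.** Degrees of freedom = 20 + 20 − 2 = 38, and the critical value is c = t(0.975; 38) = 2.024. With no true difference, P(T > c) + P(T < −c) = 0.025 + 0.025 = 0.050. This matches the stated 0.05.

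**Step 2. What the rule labels superior when there is no difference.** As written, both tails count: 0.050. If only the favourable tail counts: 0.025.

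**Step 3. What the rule labels superior when the truth favours MS6.** T is noncentral t with 38 df and noncentrality −d × √(20/2) = −3.162d. As written, the probability is P(T < −c) + P(T > c). With a direction requirement it is P(T > c) alone.

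| Assumed d favouring MS6 | Noncentrality | Labelled superior, as written | Labelled superior, direction required |
|---|---|---|---|
| 0.2 | −0.632 | 0.095 | 0.005 |
| 0.5 | −1.581 | 0.338 | 0.0002 |
| 0.8 | −2.530 | 0.693 | below 0.0001 |

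The third column also assumes that the rule is applied to the letter and the sign of the estimate is ignored.

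**Step 4. Limits of these figures.** They apply to one FC quantity. Section 2.11.1 corrects for multiple comparisons by FDR. If no connection truly differs, FDR control at 5% holds the chance of any rejection at about 5% in total, so the wrong-tail rate for each of many quantities is below 2.5%.

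**Step 5. Order of the claim.** In section 2.11.2 the sequence is: FC significant, then superior and effective, then the secondary endpoint is tested. The word effective comes before the FMA-UL and MBI results and does not depend on them.

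**The case against.** The strongest defence is that the design is declared a superiority trial (sections 1 and 2.1), and that concluding superiority from a two-sided p<0.05 is common shorthand with the favourable sign understood. A reader might infer from the literal wording that a result favouring MS6 would be reported as a win for the experimental arm. The article nowhere says so, and that intention should not be attributed to the sponsor. The shorthand still fails here, because it needs an agreed good direction and none is tied to the rule. Nor can the analyst be left to supply it: under section 2.6 the statisticians know the groups only as A and B, and are not told whether the trial is a superiority trial.

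Other stronger readings are also unsupported.

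- *The plan is silent on direction.* It is not. Section 2.8.1 links stronger FC to better behaviour, and healthy controls supply a reference. But one background sentence cannot fix the sign for every connection.
- *Motor outcomes play no part in the trial.* FMA-UL and MBI are analysed for group and time-group effects, and section 2.11.1 correlates imaging with behavioural data, so a null motor result would be visible. They play no part only in the step to effective.
- *Every FC quantity carries a 2.5% wrong-direction risk.* Step 4 shows why this fails under FDR correction.
- *A significant FC result beside a null FMA-UL result is likely.* With 20 per group, power for FMA-UL is 0.338 at an assumed 0.5 SD and 0.693 at 0.8 SD, but low FMA-UL power says nothing about how often FC is significant. The joint probability cannot exceed the chance of a significant FC result, which is 5% when FC does not differ. No FC effect size is given from which to go further.

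The conclusion is also hedged (could be considered), and in a neuromodulation trial effective might mean an FC effect. The active comparator is justified in section 1, and the lack of a sham or blank control is listed as a limitation in section 3. All of this lowers the severity. It does not make the rule correct as written.

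**Conclusion.** The rule is wrong as written, in two respects: it requires no favourable direction, and it concludes effectiveness from FC versus an active comparator independently of FMA-UL and MBI. The two-sided test is not at fault, and an FC primary endpoint is legitimate in a mechanism trial. The fault lies in the inference drawn from significance.

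The size is 5% against 2.5% of trials labelled superior when a single FC summary does not truly differ. The larger probabilities in the table depend on assumed true effects favouring MS6 and illustrate the mechanism only. None of the figures carries over directly to many FC quantities under FDR correction.

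This is a should-fix matter of wording. It does not invalidate the design, the tests or the sample size.

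**What to change.** Reword the rule in section 2.11.2, before unblinding, along these lines:

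> Superiority on the primary endpoint is concluded only if the two-sided p value is below 0.05 and the between-group difference in the primary FC measure lies in the favourable direction stated before unblinding. Connections without a pre-stated sign are reported as differences only. A result on FC alone is reported as a different FC change versus MS6. The therapy is described as more effective for motor function only if FMA-UL also differs significantly in favour of the experimental group.

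The sponsor must choose and record the favourable direction. Section 2.8.1 suggests stronger sensorimotor FC, but another may be justified.

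The cost is a few sentences, with no change to tests, data or sample size. The downside is a narrower claim if only FC differs.
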